### Assessments and Instruments

Three measurement points will be considered (Table 1). Considering the context of data gathering, care has been taken to avoid overburdening participants with excessive questionnaires. The screening will include sociodemographic data and RAG. The first assessment, before the first session, includes some additional sociodemographics, PG13-R, HADS, Brief COPE, ECR-RS, AAQ-II, and MSPSS. The second assessment will include PG13-R, HADS and the working alliance measure (WAI-S). The follow-up assessment period (3rd assessment) will occur six months after the last assessment. These will include all outcomes (PG13-R, HADS, PTGI). The interventions will share the same assessment periods and instruments. The follow-up assessment ensures that all participants are evaluated one year after the death, enabling a PGD diagnosis.

**Table 1 t1:** Time Points for Measurement

Instrument	Screening	T1	T2	6 mths
Sociodemographics	x	x		
Risk Assessment for Grief (RAG)	x			
PG-13-R		x	x	x
The Hospital Anxiety and Depression Scale (HADS)		x	x	x
The Posttraumatic Growth Inventory (PTGI)				x
Brief COPE		x		
Experiences in Close Relationships (ECR-RS)		x		
Acceptance and Action Questionnaire II (AAQ-II)		x		
The Multidimensional Scale of Perceived Social Support (MSPSS)		x		
The Working Alliance Inventory-short form (WAI-S)			x	

*Note*. T1 = Pre-treatment; T2 = 12 weeks/Post-treatment; 6 months = follow up.

Participants will be contacted sensitively to inquire about the reasons for discontinuing the intervention. Clinical teams will receive supervision for each intervention, and adherence to treatment measures will be monitored.

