### Statistical Analysis

To evaluate the impact of Empower-Grief relative to TAU on the primary outcome (prolonged grief symptoms) and secondary outcome (anxiety and depression), we will use a mixed-effects model. A mixed-effects model for longitudinal data (pre-post and a 6-month follow-up) accounts for the hierarchical structure of the data, with participants nested within treatment groups and the correlation between repeated measurements within subjects. The intention-to-treat principle will be followed in the analysis, ensuring that all participants randomized to each treatment condition are included in the analysis, regardless of whether they completed all assessments or adhered to the treatment protocol. To address missing data, multiple imputations will be employed, a statistical method that generates multiple plausible values for missing data points based on the observed data. This method preserves the relationships between variables and reduces the potential for bias due to missing data.

Before drawing inferences, a preliminary examination of model assumptions, including checks for the normality of residuals and homogeneity of variances, will be conducted. The primary outcome, prolonged grief severity, will be modelled using a linear mixed-effects model with fixed effects for treatment condition (Empower-Grief vs. TAU), time point (pre-treatment, post-treatment, and 6-month follow-up), and their interaction, and random effects for participants and treatment groups. Secondary outcomes, anxiety and depression symptoms, will be analyzed using similar mixed-effects models.

The sample size for this research project was estimated using G*Power software, employing a repeated measures analysis with a mixed-effects model. Assuming a low effect size of *d* = 0.25, a significance level of α = 0.05, and a power of 1-β = 0.80. With two treatment groups, Empower-Grief and treatment as usual, and measurements taken at three moments (baseline, post-treatment, and 6-month follow-up), the resulting estimated sample size for the study was 44 participants for both treatments, representing a robust size to detect the anticipated effect with high statistical power.

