To assess the predictive value of the considered predictors (i.e., posttraumatic growth, coping, attachment to the deceased, psychological flexibility, social support, and therapeutic alliance) on treatment outcomes, separate regression analyses will be conducted for each outcome measure (prolonged grief, anxiety, and depression). For each outcome, we will fit a mixed-effects model with the baseline variable as a fixed effect, adjusting for treatment condition, time, and their interaction. The random effects’ structure will remain the same as in the primary analysis.

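### Posttraumatic growth and working alliance are listed as baseline predictors of outcome, but neither is measured at baseline

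*Protocol article*

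**What the plan says.** All references are to the Method part of the protocol article.

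- **Predictor list (Statistical Analysis).** Six constructs are named: "the considered predictors (i.e., posttraumatic growth, coping, attachment to the deceased, psychological flexibility, social support, and therapeutic alliance".
- **Model (Statistical Analysis).** The article states that "separate regression analyses will be conducted for each outcome measure (prolonged grief, anxiety, and depression". It gives the form of the model as follows: "we will fit a mixed-effects model with the baseline variable as a fixed effect, adjusting for treatment condition, time, and their interaction". Its random-effect terms are those of the primary analysis. No predictor-by-time term is mentioned.
- **Time levels (Statistical Analysis).** The primary model uses "time point (pre-treatment, post-treatment, and 6-month follow-up), and their interaction".
- **Schedule (Assessments and Instruments).** The first assessment "includes some additional sociodemographics, PG13-R, HADS, Brief COPE, ECR-RS, AAQ-II, and MSPSS". For T2: "The second assessment will include PG13-R, HADS and the working alliance measure (WAI-S". For the 6-month follow-up: "These will include all outcomes (PG13-R, HADS, PTGI". Table 1 agrees: the WAI-S is marked only under T2 and the PTGI only under 6 months.

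**The concern.** A baseline predictor has to be known before treatment and before the response it is meant to predict. Four of the six constructs meet that condition and two do not. The PTGI also has two roles: an outcome in the assessment section and a predictor in the analysis section.

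What is at stake is the trial's second objective, identifying predictors of response. People whose grief eases may report more growth or a better alliance because it eased. A coefficient from the stated model cannot separate that from prediction. Both measures are also taken after randomisation and may differ by arm, so entering them beside treatment raises the question of which treatment terms they disturb.

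**Working it through.** The plan gives no figure to reproduce. The check sets the predictor model against the schedule.

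**1. Time order**

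| Predictor | Collected | vs T1 outcome | vs T2 outcome | vs 6-month outcome |
|---|---|---|---|---|
| Brief COPE, ECR-RS, AAQ-II, MSPSS | T1 | same visit | earlier | earlier |
| WAI-S | T2 | later | same visit | earlier |
| PTGI | 6 months | later | later | same visit |

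Four of six constructs have a T1 value; two of six do not. The PTGI is earlier than 0 of 3 outcome measurements, and the WAI-S is earlier than 1 of 3.

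**2. What the coefficient would measure**

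The predictor is constant within a person and has no interaction with time. With complete data and a random intercept, its coefficient is the association with the person's mean outcome over the three visits:

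b = (b_T1 + b_T2 + b_6m) / 3

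where each term is the arm-adjusted slope at that visit. For the PTGI, two of the three terms relate to scores recorded before it and none to a score recorded after it. For the WAI-S, only b_6m is in the predictive direction, and it carries one third of the weight.

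**3. How easily a consequence could look like a predictor (illustration)**

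The correlations here are assumed; the article gives none. Suppose the later measure is purely a consequence of an earlier outcome, with N = 44 and a two-sided 5% test. In 4,000 simulated trials per setting, it was significant in about 5% at correlation 0, 52% at 0.3 and 94% at 0.5.

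**4. Effect on the treatment terms**

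*Treatment-by-time contrasts.* With complete data these are estimated from within-person changes. A covariate that is constant within a person cancels from every change score, so the contrasts are the same with or without it. A simulation under assumed values (22 per arm, predictor affected by both arm and 6-month outcome) agreed: the 6-month contrast averaged -0.511 in both models, with no difference in any run. With 20% of T2 and 6-month outcomes missing at random, the averages were -0.477 and -0.479, and the largest shift in a single run was 0.10.

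*Arm main effect.* This does move. In the same complete-data simulation it went from -0.01 to 0.36.

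*Arm difference read at a single visit.* Assume the predictor is x = a·g + 0.5u + e and the outcome is y = -0.5g - 0.5u + e', where g is arm, u is an unmeasured common cause with variance 1, and e and e' are independent with variance 0.75. Within arm, cov(x, y) = -0.25 and var(x) = 0.25 + 0.75 = 1, so the slope on x is -0.25. The adjusted arm difference is -0.5 + 0.25a:

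- a = 0.5: -0.375 (simulated -0.38)
- a = 0.8: -0.30 (simulated -0.29)

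That shift concerns an adjusted difference at one time point. It does not carry over to the treatment-by-time contrasts.

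**The case against.** **Baseline variable may mean the baseline score of the outcome.** The wording allows this. Growth and alliance would still be listed predictors in a model spanning visits that come before them.

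**Alliance can only be measured once therapy has begun.** This stands. The conclusion of the abstract gives understanding how the interventions operate as an aim, and T2 alliance may properly be related to the 6-month outcome. The difficulty with the WAI-S is its use for T1 and T2 scores. The article states no restriction to the later visit.

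**The trial is exploratory and the efficacy analysis is separate.** Both are true and limit the importance of the point. They do not turn a later measurement into a baseline one.

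A reader might also infer more than the documents support:

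- *That the randomised comparison is broken.* The efficacy model contains no predictors, and in the predictor models the treatment-by-time contrasts are unchanged under the conditions shown above.
- *That the associations will be reverse-causal.* This is a possibility the design cannot exclude, not a certainty.
- *That at least six models are affected.* The article promises separate regressions for each of three outcomes and does not say one model per predictor.
- *That the authors would choose treatment by growth or alliance.* The factors the Background names for adapting the intervention include neither, and the Discussion names psychological flexibility and attachment as examples.
- *That the heading over the PTGI description makes it a predictor.* That heading also covers other relevant variables; the predictor label comes from the Statistical Analysis section.

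**Conclusion.** The point holds for two of the six listed predictors, across all three outcomes. As written, the baseline-predictor analysis does not fit the article's own schedule: the PTGI cannot precede any scheduled outcome, and the WAI-S can precede only the 6-month one. Associations with earlier or same-visit scores should not be reported as prediction of response. The PTGI's two roles need to be reconciled.

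The defect is confined to the second objective of an exploratory trial, and the primary and secondary efficacy analyses are untouched. Within the predictor models, the arm main effect, and any single-visit arm difference built from it, can shift. The statement that the treatment-by-time contrasts do not shift assumes complete data and no predictor-by-time term. The timing result rests on the article's text and Table 1 alone. The percentages and shifts in the working depend on assumed values and show direction only. This should be corrected before analysis, but it does not threaten the main result.

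**What to change.** 1. Restrict the baseline-predictor models to the four T1 measures: Brief COPE, ECR-RS, AAQ-II and MSPSS.
2. Remove posttraumatic growth from the predictor list. Name the PTGI as a 6-month outcome and compare it between arms at that visit.
3. Take the WAI-S out of the baseline-predictor models. If it is kept, relate T2 alliance to the 6-month outcome only, adjusting for arm and for the T1 and T2 scores of that outcome. Describe it as a post-randomisation process variable and report the result as non-causal.
4. Take treatment effects from the efficacy model only, never from a model that contains the PTGI or WAI-S.

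The cost is a change of wording, with no new data or visits. There are two fewer baseline predictors to report, and the alliance analysis will be imprecise with 44 participants (44 / 2 = 22 per arm if allocation is equal).

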## Abstract

**Background:**

Grief reactions of relatives of palliative care patients are seldom addressed. Most interventions focus on Prolonged Grief Disorder (PGD) and not on its prevention. This is particularly relevant in palliative care, in which death is the result of a difficult period of a terminal illness, making caregivers particularly vulnerable to psychological distress. The purpose of the present exploratory trial is to test the efficacy of a selective intervention (Empower-Grief) for the initial problematic grief reactions and to study potential predictors of adherence and efficacy.

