The majority of the family caregivers will require selective intervention, oriented at people identified as being at risk of developing PGD. The differentiation of interventions allows combining need-based timely interventions to prevent PGD while increasing access through rationalization of service delivery. Despite the recommendations, no studies have matched the intensity of interventions to the severity of psychological reaction to death in preventing prolonged grief. The present research intends to implement and evaluate the effectiveness of the Empower-Grief intervention (Coelho et al., 2024; Lichtenthal et al., 2022) in the population of family caregivers of patients accompanied in the Palliative Medicine Unit of the Centro Hospitalar Universitário Lisboa Norte (CHULN). Empower-Grief is an adaptation of the original EMPOWER to the current palliative care context and post-mortem stage. It consists of the same six modules of the original intervention, but a 50-minute session is devoted to each of the modules, with two booster sessions done after treatment. It is a manualized treatment in which each session is structured.

This research project has two objectives. First, to evaluate the effectiveness of Empower-Grief Intervention compared to treatment as usual (TAU) in terms of symptoms of prolonged grief and psychological distress in relatives or caregivers of palliative and oncological patients. The second objective is to identify predictors, among the factors consistently found in the literature, of response to intervention. This second objective is crucial, considering the low-intensity level of the intervention. In addition to the risk of prolonged grief, other factors such as prior mental health, the nature of the death, social support, attachment style and psychological flexibility may be relevant in explaining the response to this intervention and serve as essential variables in adapting the intervention to the needs of the participants. This research is crucial to influence national policy towards a greater emphasis on prevention and early intervention, making the allocation of cost-effective bereavement support services the most efficient and sustainable approach for a significant public health impact in bereavement care.

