## Discussion

This study responds to a lack of research in grief interventions, which is relevant considering the high prevalence of PGD and the general delay in providing care. Assessing the differentiation of intervention leads to increases and equality in access to empirically based interventions. By empowering caregivers to respond to a challenging grief process, the intervention may contribute to preventing pathological long-term psychological reactions. The present research project aims to assess the efficacy of a low-intensity selective intervention compared with TAU in terms of prolonged grief symptoms and distress. The project's second goal is to identify potential predictors of the outcome and adherence to these treatments – considering the matching conditions.

This research has several strengths. First, the study of low-intensity interventions – recommended by international and national bodies (Shear et al., 2017) – has a good cost-benefit ratio and increases access to psychological interventions in this social context. Second, Empower-Grief is flexibly delivered so that it can be adapted to caregivers’ dynamic needs and post-mortem context. Third, it was developed and refined using stakeholder feedback to optimize its acceptability and fit for its recipients’ specific needs. Also, identifying predictors of adherence and change serves to increase sensitivity in aligning interventions to the needs of clients.

The fact that the current study is conducted in a practice setting leads to some constraints – namely, the lack of manualization of TAU or the need to keep the research questionnaire relatively small. However, the practice-based nature of the context of data gathering provides a demonstration of how a structured intervention such as Empower-Grief can be useful. Results from this study will, therefore, provide a pathway for improving clinical decision-making and tailoring treatments to an individual's specific needs, which is crucial to meeting citizens’ needs in the context of the rational provision of services.

This research is situated in the field of intervention personalization and psychological services research. It can inform and enrich the predicting process by considering other dimensions of patient characteristics, such as psychological flexibility or attachment, thus fostering new research and informing bereavement support practice.

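### The predictor analysis only partly covers the second objective: entry risk and prior mental health are left out, adherence has no model, and two later measurements are treated as baseline variables

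*Protocol article*

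**What the plan says.** **The aims.** The Background states: "The second objective is to identify predictors, among the factors consistently found in the literature, of response to intervention". It then gives candidates: "In addition to the risk of prolonged grief, other factors such as prior mental health, the nature of the death, social support, attachment style", with psychological flexibility closing the series. All are described as possibly relevant. The Abstract puts the purpose more widely, "to study potential predictors of adherence and efficacy", and the Discussion repeats this: "The project's second goal is to identify potential predictors of the outcome and adherence to these treatments".

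**The analysis.** The Statistical Analysis section defines the predictors as "i.e., posttraumatic growth, coping, attachment to the deceased, psychological flexibility, social support, and therapeutic alliance". For the outcomes it says that "separate regression analyses will be conducted for each outcome measure (prolonged grief, anxiety, and depression" are the measures concerned. Each model enters the predictor, called the baseline variable, as a fixed effect, adjusted for arm, time and arm-by-time. No term crosses the predictor with time or with arm.

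**The data.** Under Assessments and Instruments and Screening, the RAG and the mental health and treatment history are taken at screening. Reasons for discontinuing are sought and adherence is monitored, though no adherence measure is defined. Table 1 places the Posttraumatic Growth Inventory (PTGI) at 6 months only and the alliance inventory (WAI-S) at T2 only. The text above the table counts PTGI among the outcomes.

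**The concern.** The list is introduced as a definition, not as examples, so an analyst who follows it would leave out RAG and mental health history although both are in the data set. The article presents this objective as especially important because the intervention is of low intensity, and its rationale is to fit intensity of support to severity. Entry risk is then the first characteristic that a reader would expect to see related to response.

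The same analyst would fit nothing with adherence as the outcome, although the Discussion counts knowledge of who adheres among the study's strengths.

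The list also admits two variables that are not known at baseline. A 6-month PTGI score is recorded together with the last outcome it is meant to predict, and alliance is rated after treatment has been delivered. Reporting either as a baseline predictor would present a concurrent or post-treatment association as prospective prediction.

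**Working it through.** The plan states no figure for this analysis, so the check is mainly a comparison of its sections.

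**1. Factors named with the second objective (Background) against the predictor list (Statistical Analysis)**

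| Factor | Collected | On the list |
|---|---|---|
| Risk of prolonged grief | RAG, screening | No |
| Prior mental health | History, screening | No |
| Nature of the death | No measure in Table 1 | No |
| Social support | MSPSS, T1 | Yes |
| Attachment | ECR-RS, T1 | Yes |
| Psychological flexibility | AAQ-II, T1 | Yes |

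Coverage is 3 of 6. Of the three omitted, two could be analysed with data in hand.

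**2. Targets of prediction.** The Abstract and Discussion name two: efficacy (outcome) and adherence. The section models prolonged grief, anxiety and depression, so the first is covered and the second is not.

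**3. Timing of the six listed predictors (Table 1)**

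| Predictor | Measured |
|---|---|
| Coping, attachment, flexibility, support | T1 |
| Therapeutic alliance (WAI-S) | T2 only |
| Posttraumatic growth (PTGI) | 6 months only |

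Four of six are baseline variables; two are not.

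**4. What the model estimates.** A predictor entered only as a main effect describes the outcome level averaged over the three time points, the pre-treatment one included. Response is change, so a predictor-by-time term is needed. A difference in response between arms would need arm in that term as well.

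**5. Precision of an added arm interaction.** Assumptions: the 44 participants split 22 and 22, no missing data, residual SD 1, predictor scaled to SD 1 in each arm. Each arm's slope then has variance of about 1/22.

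- SE of the difference in slopes = √(1/22 + 1/22) = √0.0909 = 0.30
- 95% half-width = 1.96 × 0.30 = 0.59 SD of outcome per SD of predictor

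Per raw point of RAG, the SE is 0.30 divided by the SD of RAG among those enrolled. Anything that narrows the range of RAG widens the interval per point.

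**6. Information on adherence.** The article gives no discontinuation rate. Assuming 10%, 20% or 30% of 44 gives 4.4, 8.8 or 13.2, that is about 4, 9 or 13 events. None of these supports a regression on several predictors at once.

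**The case against.** The other side has a fair case.

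- **The Background wording is hedged.** Factors that may be relevant are not a commitment to model each one. This stands, and it limits the RAG and mental health gap to a mismatch between aim and analysis. The adherence aim in the Abstract and Discussion is not hedged in this way.
- **An article condenses.** An adherence analysis may exist in a fuller plan, and the section shown speaks only of treatment outcomes. This stands in part: adherence may be covered elsewhere. It does not help the predictor list, which is closed, or the timing of PTGI and WAI-S, which the article itself fixes.
- **Eligibility narrows the added predictors.** Only RAG scores of 7 or more are invited, and severe or active mental disorder predating the loss is excluded. This stands: the added estimates will carry limited information.
- **The yield is small.** An interval of ±0.6 SD would not settle whether response differs by risk. This also stands, and it is a reason to report descriptively. It applies equally to the predictors already listed.

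A reader might infer that testing the effect by entry risk is a stated aim. It is not: the remark about matching intensity to severity is rationale, and the stated aim is predictors of response. A reader might also infer that the trial plainly enrols both moderate-risk and high-risk people. The text is ambiguous. The recruitment section gives a threshold of 7 or more but refers to a moderate level, and the RAG section places a score of 10 in both the moderate and the high band. Those passages need to be reconciled.

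**Conclusion.** The concern holds as a matter of incomplete coverage. Three of the six factors named with the second objective are analysed. Two of the other three are collected but left out of a closed list, and one has no measure. Adherence is a stated target of prediction with no model in the article. Two of the six listed predictors are measured after baseline, and one of those is an outcome by the article's own account.

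It would go too far to conclude that the second objective cannot be answered. Social support, attachment, flexibility and coping are all measured at T1 and set against all three symptom outcomes. Nor is adherence a predictor that was forgotten: it is something to be predicted and needs its own model.

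The consequence is confined to an exploratory secondary aim. The primary comparison is untouched. The ±0.6 SD figure rests on the assumed equal split, complete data and unit scaling.

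**What to change.** In the Statistical Analysis section:

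1. Add RAG total, as a continuous score, and mental health history to the exploratory predictor list. Include terms with time, and with arm as well if differential response is of interest.
2. Remove PTGI from the predictors and report it as an outcome.
3. Keep WAI-S if wanted, labelled as a post-baseline process variable whose association is not prediction from baseline.
4. For adherence, define the measure from the adherence and discontinuation data already monitored and fit one descriptive exploratory model with few predictors. Otherwise, remove adherence from the aims in the Abstract and Discussion.
5. Drop nature of the death from the objective, since Table 1 lists no measure of it.

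No new instrument, visit or participant is needed, although the article does not say in what form adherence is recorded, so that must be confirmed first. The article describes the trial as ongoing with data analyses still to be completed, which leaves room to amend the plan before results. The cost is a few more exploratory estimates. They will be imprecise with 44 participants and with eligibility narrowing RAG and mental health history, so they should be reported with intervals and described as descriptive.

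### The predictor models have only a main effect of each predictor on all three visits, pre-treatment included, so they measure association with average symptom level and not response to the intervention

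*Protocol article*

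**What the plan says.** **The aim.** The Background section of the protocol article gives the second objective as "to identify predictors, among the factors consistently found in the literature, of response to intervention", and says such factors may "serve as essential variables in adapting the intervention to the needs of the participants". The abstract states the purpose as "to study potential predictors of adherence and efficacy". The Discussion is mixed: it says the goal is to "identify potential predictors of the outcome and adherence to these treatments", and when listing the study's strengths it speaks of predicting adherence and change.

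**The model.** The last paragraph of Statistical Analysis lists six predictors: posttraumatic growth, coping, attachment to the deceased, psychological flexibility, social support and therapeutic alliance. There is to be a separate analysis for prolonged grief, anxiety and depression, and in each "we will fit a mixed-effects model with the baseline variable as a fixed effect, adjusting for treatment condition, time, and their interaction". Nothing changes in how random effects are handled relative to the main model.

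**The outcome vector.** The primary model in the same section has fixed effects for treatment condition, "time point (pre-treatment, post-treatment, and 6-month follow-up), and their interaction". The pre-treatment score (T1) is thus a response and not a covariate. The predictor models are described in the same terms, so the interaction they mention is treatment by time. No term lets the predictor's effect vary by time or by arm.

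**The concern.** Response means change after treatment starts. Tailoring asks whether that change depends on the trait differently under Empower-Grief and under TAU. A single coefficient for the predictor, shared by all visits and both arms, measures neither directly.

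Many of these traits (attachment anxiety, psychological inflexibility, poor social support) could plausibly go with more grief at every visit, including the visit before any treatment. Such a trait would be reported as a predictor of treatment outcome although it says nothing about who improves. A trait that helps in one arm and hinders in the other would be missed. The article wants these results to inform the tailoring of bereavement support, so the mislabelling would matter.

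**Working it through.** **Plan's own figure.** The article gives no power or precision for the predictor models. Its 44 participants were calculated for the primary comparison; that number is taken as given here. Every correlation and slope below is an assumption.

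**Step 1: what the coefficient estimates.** Take a predictor that is constant over time, complete data and a random intercept per participant. Let b1, b2 and b3 be the predictor's slopes on the outcome at T1, T2 and 6 months, averaged over arms. The planned coefficient is (b1 + b2 + b3)/3.

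| Type of predictor | Slopes | Planned coefficient |
|---|---|---|
| Level only | 0.5 at every visit | (0.5 + 0.5 + 0.5)/3 = 0.50 |
| Change, same in both arms | 0, then 0.5 and 0.5 | (0 + 0.5 + 0.5)/3 = 0.33 |
| Change under Empower-Grief only | 0, then -0.5 in one arm | (2/3) x (1/2) x (-0.5) = -0.17 |
| Change of opposite sign by arm | 0, then -0.5 and +0.5 | 0 |

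A large-sample simulation (200,000 participants) of rows 1, 3 and 4 gave 0.50, -0.17 and 0.00. The predictor-by-treatment slope on T2 minus T1 change was 0.00, -0.50 and -1.00.

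**Step 2: a level-only trait with 44 participants.** Let the trait correlate r with the outcome at each visit, and let rho be the correlation between visits. The mean of three visits has variance (1 + 2 rho)/3, so the trait correlates R = r / sqrt((1 + 2 rho)/3) with that mean. The expected t is about R x sqrt(41) / sqrt(1 - R^2), against a critical value of 2.02.

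- r = 0.4, rho = 0.4: R = 0.516, t = 3.86, rejection about 97%
- r = 0.4, rho = 0.6: R = 0.467, t = 3.38, rejection about 91%
- r = 0.3, rho = 0.8: R = 0.322, t = 2.18, rejection about 56%

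Simulation (3,000 trials per cell) agrees:

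| Planned test rejects | rho 0.4 | rho 0.6 | rho 0.8 |
|---|---|---|---|
| r = 0.4 | 96% | 90% | 83% |
| r = 0.3 | 74% | 67% | 56% |

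Repeat runs differ by one or two points. Tests of the predictor on change, and of predictor by arm, reject in 4 to 6%.

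**Step 3: a trait that does predict change, equally in both arms** (rho = 0.6). With a slope of 0.5 SD the planned test rejects in 67% and a change test in 97%. With 0.3 SD the figures are 31% and 68%.

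**Step 4: a trait whose effect differs in sign by arm.** The planned test rejects in about 6%, close to its nominal level. A predictor-by-arm test on the baseline-adjusted outcome rejects in 97 to 99.9% at +/-0.5 SD, but only about 54 to 83% at +/-0.25 SD. On change scores (mean of T2 and 6 months, minus T1) power at +/-0.25 SD is about 37 to 79%. These ranges are for rho 0.4 to 0.8.

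**Step 5: precision of the remedy.** The slope difference between arms in T2 minus T1 change that 44 participants detect with 80% power is (1.96 + 0.84) x sqrt(2(1 - rho)) x sqrt(4/44). This is about 1.00, 0.85 and 0.65 outcome SD per predictor SD for rho 0.3, 0.5 and 0.7. An effect of +/-0.25 SD is a difference of 0.50, below all three.

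**The case against.** **The aim can be read as prognostic.** The paragraph that introduces these models speaks of treatment outcomes, and the Discussion says "identify potential predictors of the outcome and adherence to these treatments". On that reading a predictor main effect adjusted for arm and time is a common, if blunt, choice. This softens the point but does not remove it. With T1 among the outcomes the coefficient is not a clean prognostic effect either, and the Background and abstract ask about response and efficacy.

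**The model is not blind to response.** A reader might infer that it cannot pick up any predictor of response, or that the second objective must come out wrong even with perfect data. The stated model does not support that. A predictor of change in both arms moves the coefficient at two thirds of its size (Step 3). The model is inefficient and non-specific for such predictors; it is blind only where effects cancel.

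**The contrast can be oversold.** A reader might take about 6% against about 99% as what the change would gain. That needs a slope difference of a full SD with exact reversal of sign, which is an extreme case.

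**The trial is exploratory and the article is condensed.** Exploratory status excuses low power, but not a coefficient that measures something else. Nor is this a detail left to another document, since the article writes the model out. The phrase about the baseline variable could mean the baseline outcome score, but the sentence before it is about the predictors, and on that reading no predictor would be in the model.

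**Conclusion.** The point holds in a bounded form. As written, the predictor coefficient is an association with average symptom level over three visits, one of them before treatment. It does not separate level from change, it dilutes prediction of change to two thirds, and it misses effects of opposite sign by arm. That follows from the model and does not depend on the sample size.

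The size depends on assumptions. A level-only trait with r of 0.3 to 0.4 is flagged in about 56 to 96% of trials of 44 participants when the within-person correlation is 0.8 to 0.4, against about 5% for a change test. The article gives none of these correlations.

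This should be fixed before the analysis. It concerns the second objective of an exploratory trial; nothing here touches the primary treatment comparison, and a reader should not extend it there.

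**What to change.** 1. For the predictors that Table 1 places at T1 (coping, attachment, psychological flexibility, social support), keep all three time points. Add predictor by time, predictor by treatment, and predictor by treatment by time.
2. State which term answers which question: predictor by time for change, the three-way term for differential response. Base conclusions about response on these interactions with time and not on the predictor main effect.
3. A model of the T2 and 6-month scores adjusted for T1, with predictor by treatment, is an acceptable alternative for moderation only. It is not equivalent to item 1. Its predictor main effect must not be read as prediction of change, because one T1 score does not remove stable level: at r = 0.4 that term still flags a level-only trait in 19 to 66% of trials.
4. Table 1 has the PTGI at 6 months only and the WAI-S at T2 only. Do not analyse or report them as baseline predictors of response.
5. Label all these results exploratory and report interval estimates.

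**Cost.** A few model terms and some sentences; no new data. The downside to state openly is imprecision: with 44 participants, moderate interactions will often be missed (Steps 4 and 5), so a null result will not show that a trait is irrelevant to tailoring.
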